Interventional, multicentre nationwide single blinded randomized controlled trial. Preterm infants entering the trial will receive either routine medical care plus osteopathic evaluation and treatment or routine medical care plus osteopathic evaluation only (figure 1).

Participating NICUs

Patients will be recruited from three Italian secondary and tertiary NICUs at the public hospital in Pescara, Macerata and Monza.

The three participating NICUs are located throughout Italy in urban regions with catchment areas of about 40 000 to 150 000 inhabitants. Principal investigators of the participating NICUs are neonatologists and osteopaths with at least 5 years of osteopathic treatments in NICU and specialized neonatal osteopathic education.

Population

Participants who met the following inclusion criteria are considered eligible for the trial: male and female preterm infants entering the NICUs in the period between 1 July 2012 and 30 June 2013, preterms born in the same hospital of the referred NICU and free of medical complications and parents or legal guardian written informed consent.

Subjects presenting the following clinical conditions are excluded:

- gestational age <29 weeks
- gestational age >37 weeks
- first OMT performed after 14 days from birth
- genetic disorders
- congenital disorders
- cardiovascular abnormalities
- proven or suspected necrotized enterocolitis with or without gastrointestinal perforation
- proven or suspected abdominal obstruction
- pre/post surgery patients
- pneumoperitoneum
- atelectasis
- newborn from an HIV seropositive/drug addicted mother
- respiratory disorders
- transferred to/from other hospital
- admitted for preterminal comfort care (defined as neither intubation nor cardio-respiratory resuscitation)

Randomization process

All patients entering the study are sequentially allocated to the experimental and control arms using R (R core team, Vienna, Austria), an open source statistical software, as computer random number generator 18.

The type of randomization procedure is permuted-block (ratio 1:1).

The process of randomization is performed in the coordinating center.

Research investigators

Investigators will be grouped into three groups:

1. “consultant performing the randomization”
2. “osteopaths performing the evaluation”
3. “osteopaths performing the evaluation&treatment”

Consultant performing the randomization

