Data export will take place at the end of the study by the statistician from the coordinating center European Institute for Evidence Based Osteopathic Medicine (EBOM).

Measurements

To evaluate the effect of the treatment, standard measurements will be recorded. Data will be collected at the baseline (entry time, T0), every time the osteopathic service is provided and at the end of the stay in the unit (discharge time, T1). An expected average period of 4 weeks has been considered.

The following measurements will be included for the primary and secondary outcomes.

Primary outcome: length of stay (LOS)

LOS will be used as primary outcome and measured as the mean difference in days between T1 and T0.

According to international guidelines, the following physiological conditions are required for discharge: maintenance of body heat at room temperature, coordinated sucking, swallowing, and breathing while feeding; sustained pattern of weight gain; stability of cardiorespiratory function (no episodes of apnea/bradycardia for 2-5 days, free of supplemental oxygen support) 8.

Secondary outcomes

Secondary outcome measurements include the following parameters:

1. daily weight gain, referred as the net weight variation per day expressed in grams
2. episodes of vomit, the number of vomits per day
3. episodes of regurgitation, the number of regurgitations per day
4. episodes of stooling, the number of stools per day
5. use of enema, the number of enemas used per day
6. time to reach full enteral feeding, the number of days before autonomous feeding is achieved
7. NICU costs, calculated as NICU daily newborn expenses, according to local authorities, multiplied by the newborn’s LOS. Costs will be estimated in euros per day
8. side effects of treatment (osteopathy and clinical procedures)

In addition to these measurements, socio-demographic and clinical data will be collected and include:

1. newborn’s data: gender, gestational age, weight at birth and at entry, height, head circumference at birth, route, type and length of delivery, diagnosis at T0 and T1, associated pathologies
2. mother’s data: age, ethnicity, BMI, nationality, number of previous pregnancies, clinical medical condition during pregnancy, concurrent pathologies
3. father’s data: age, ethnicity, BMI, nationality, concurrent pathologies

Statistical analyses

All calculations will be performed at the coordinating center EBOM.

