Statistical analyses will take into account the intention-to-treat analysis. Missing data will be handled using last observation carried forward (LOCF) imputation technique. Arithmetic means and standard deviation will be used for the general characteristics of the study population. Univariate statistical tests will be performed to compare the experimental group and control group at the baseline. A generalized linear model, linear regression, will be considered to study the independent effect of OMT on primary endpoint and secondary endpoints, taking into account all possible confounders. The significance level will be at α=0.01. Differences between the groups will be presented as mean with 95% CI or in categories with OR for categorical data.

The statistical program in use for randomization and data analyses is R 18.

Sample size

Sample size calculation used an effect size of 0.3 calculated from previous studies, considering a mean difference of 4 days between experimental and control group and a SD of 14. The statistical power is set at 0.90 and an alfa level equal to 0.01. This produces a sample size of 333 per group. To prevent loss of power, the sample size is increased up to 345 subjects per group. The whole sample (N=690) is then divided, with a final result of N=230 preterm infants for each NICU. A longer period of study enrollment has been considered a strategy to achieve the estimated sample size.

Coordinating center

The coordinating center EBOM consists of an executive division, President and Vice-President, an administration office, a group of researchers, an information technology consultant and a senior biostatistician.

The coordinating center collaborates with the A.I.O.T. - Accademia Italiana Osteopatia Tradizionale.

ETHICS AND DISSEMINATION

During the routine initial post-delivery consultation, the neonatologist approaches parents or legal guardians explaining the patient information sheet. Written informed consent will be then obtained from the above-mentioned guardians at study enrollment. Participation is voluntary and data collected will be sent to the coordinating centre using an anonymous identification for each patient.

The trail is approved by the ethical committee of Macerata hospital (n°22/int./CEI/27239) and it is under review by the other regional ethics committees. Moreover the trial has been registered on clinicaltrial.gov (identifier NCT01645137).

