The expected disadvantages for the intervention provided in the trial are null as well as no potential side effects due to osteopathic care are predicted as shown by the recent osteopathic literature 19. However, any side effect will be recorded during the study period and appropriately discussed in the final paper.

Publication policy

The results of the trial will be published in peer-reviewed journals and presented at relevant congresses. The trial will be reported in accordance with the CONSORT recommendations.

DISCUSSION

The purpose of this multicentre single blinded RCT is to confirm the benefits of OMT in the care of preterm infants. In this trial, osteopathic care is not based on a predetermined protocol but on needs-based approach. Thus subjects can potentially be exposed to different techniques, leading to inter-subjects and intra-subjects OMT variability. Nevertheless the objective is to provide evidence of the impact of osteopathic approach rather than the association with a given manual protocol.

On the basis of quantitative data, the scope is to estimate the effect of OMT across different centers, proving generalizability on the effectiveness of osteopathy in NICUs. Well-designed researches are scarce in the osteopathic area, thus the present study will provide the most convincing evidence of relationship between exposure and effect.

To the best of our knowledge, this will be the first study in osteopathy applied to infants using gold standards methods that include a randomized multicentre approach, a single hub computer-based data collection and a large sample size stratified by risk factors. In addition to this, the statistics that will be used will be aimed to consider different sources of variability, to allow reliable results for the effectiveness of OMT. Finally, the expected benefits for the intervention provided in the trial are shorter period of hospitalization and improvements in the secondary outcomes, leading to enhanced quality of health service delivered and cost reductions.

Authors’ contribution

CF, PG and BG conceptualized, designed and wrote the protocol. RC, D’IC, FP, PFP and TL review the protocol for important intellectual content. All authors read and approved the final manuscript.

Financial statement: This research received no specific grant from any funding agency in the public, commercial or not-for-profit sectors.

Conflict of interest: Authors declare no conflict of interest.

Ackownledgments

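### Twins and other multiples can enrol, but the only model named has no family term and no sibling link is listed; the cost is modest precision if siblings are allocated singly, and a standard error that is too small if they share an arm.

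*Protocol*

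**What the plan says.** - **Model.** Statistical analyses names one model, for the primary and secondary endpoints alike: "A generalized linear model, linear regression, will be considered to study the independent effect of OMT", adjusted by "taking into account all possible confounders". No random effect, cluster term or robust standard error is mentioned.
- **Population.** Eligibility covers "male and female preterm infants entering the NICUs in the period between 1 July 2012 and 30 June 2013". Multiple birth is not among the exclusions.
- **Allocation.** Randomization process says: "All patients entering the study are sequentially allocated to the experimental and control arms using R". The method is permuted block, 1:1. The block size is not given, and nothing says what happens when siblings enter together.
- **Data.** Measurements lists, for the mother, "age, ethnicity, BMI, nationality, number of previous pregnancies" and her medical conditions. It names neither plurality nor a link between siblings. Ethics and dissemination describes an anonymous identifier for each patient.
- **Stated intent.** The Discussion says that "the statistics that will be used will be aimed to consider different sources of variability", without naming a method.

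**The concern.** Co-multiples share a mother and a gestational age, so their lengths of stay (LOS) are likely to be correlated. A regression that treats all 690 infants as independent ignores this, and the consequence depends on how siblings fall between the arms.

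- **Split pairs** carry a within-family contrast that plain regression does not exploit, so precision is lost.
- **Pairs kept in one arm** carry less information than two unrelated infants, so the reported standard error is too small.

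The Protocol does not settle which situation applies. Without a sibling link in the data, a later analysis could not reliably separate the two or correct for either.

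**Working it through.** **The plan's own figure.** With effect size 0.3, two-sided alpha 0.01 and power 0.90, n = 2(2.576 + 1.282)²/0.3² = 331 per group. The t-based version gives 332.3, so 333 as stated. The Protocol does not state sidedness; the two-sided test reproduces its number.

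**Baseline for this point.** With 345 per group and SD 14, SE = 14 × √(2/345) = 1.066 days. For 4 days, 4/1.066 = 3.753, and power = Φ(3.753 − 2.576) = 0.88. The gap from 0.90 arises because 4/14 = 0.286 was rounded up to 0.3; unrounded, 365 (normal) or 367 (t) per group are needed. That is a separate sample-size matter.

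**Assumed inputs, none in the Protocol.** p = share of infants in twin pairs; r = residual within-pair correlation of LOS; q = probability that a pair is split between arms.

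**Formulas.**
- Information with a family term, relative to the variance plain regression reports: I = (1 − p) + p[(1 − q)/(1 + r) + q/(1 − r)].
- True variance of plain regression relative to the variance it reports: V = 1 + p·r·(1 − 2q).

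**Siblings allocated independently (q = 0.5).** V = 1, so plain regression keeps its nominal alpha.
- p = 0.2, r = 0.3: I = 0.8 + 0.2 × (0.5/1.3 + 0.5/0.7) = 1.020; SE 1.056; power 0.888.
- p = 0.2, r = 0.5: I = 0.8 + 0.2 × (0.5/1.5 + 0.5/0.5) = 1.067; SE 1.032; power 0.903.
- Upper corner, p = 0.3, r = 0.7: I = 1.288; SE 0.939; power 0.954.

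**Siblings adjacent in blocks of four (block size assumed).** Three of four adjacent positions lie within a block (split with probability 2/3) and one spans two blocks (1/2), so q = 0.75 × 2/3 + 0.25 × 1/2 = 0.625. At p = 0.2, V = 0.985 (r = 0.3) or 0.975 (r = 0.5), so plain regression is slightly conservative. I = 1.036 or 1.100. Against the true variance of plain regression, the gain is I × V = 1.021 or 1.073, again about 2% to 7%.

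**Siblings in the same arm (q = 0), p = 0.2.**

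| r | V | True SE of plain regression (reported 1.066) | True alpha at nominal 0.01 | SE with family term | Power with family term |
|---|---|---|---|---|---|
| 0.3 | 1.06 | 1.097 | 0.012 | 1.091 | 0.862 |
| 0.5 | 1.10 | 1.118 | 0.014 | 1.103 | 0.853 |

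At p = 0.3 and r = 0.7, V = 1.21 and true alpha is 0.019. Here the family term widens the reported interval, as it should.

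**If co-twins go home together.** Joint discharge would pull the difference within a split pair towards zero, and a family term gives split pairs more weight. Take p = 0.2, r = 0.5, q = 0.5, and assume for illustration that the effect is halved in split pairs. Their weight rises from 0.10 to 0.2 × (0.5/0.5)/1.067 = 0.1875. The expected estimate is 4 × (1 − 0.05) = 3.80 days under plain regression and 4 × (1 − 0.094) = 3.63 days with the family term. Power is 0.84 and 0.83, so on that assumption the gain is gone.

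**The case against.** **No error is stated.** Individual randomisation keeps plain regression valid, the model is only to be considered, and a statistical analysis plan that is not shown could add a family term. This largely stands: the Protocol rules out no such term, and its remark on sources of variability is too general to be contradicted. However, a model has been named, and a later plan cannot reliably fit a term for mother unless siblings can be linked. The list in Measurements may not be exhaustive, but it shows no such link.

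**The plan's own adjustment may do more.** The Introduction says LOS is strongly associated with gestational age and birth weight, and both are collected. Reaching power 0.90 at 345 per group needs 1.057 times the information, so covariates explaining 1 − 1/1.057 = 5.4% of LOS variance would suffice. At an assumed 10%, power is 0.92. Adjusting for gestational age, which siblings share, also lowers r. This stands, and it is why the power figures above apply only before adjustment.

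**The gain may be attenuated by joint discharge.** The arithmetic is right, but the Protocol says nothing about joint discharge and the halving is an assumption. It limits what can be promised on precision. It does not remove the need to account for siblings who share an arm.

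**Conclusion.** The point holds as a modest one. Siblings can enrol, no allocation rule covers them, the named model has no family term, and no link is listed. With infant-by-infant allocation, which is the most natural reading of the Protocol, plain regression is valid. A family term then adds about 2% to 7% information at 20% twins and residual correlation 0.3 to 0.5, and less if co-twins leave together. If siblings share an arm, the direction reverses and the reported standard error is too small.

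A reader might infer four stronger things that the document does not support:
- **That the primary analysis is invalid.** Under individual allocation, alpha is at or slightly below 0.01.
- **That the omission explains power of 0.88 rather than 0.90.** That comes from rounding 4/14 to 0.3.
- **That a large gain is assured.** The 29% at p = 0.3 and r = 0.7 rests on high assumed values, and the Protocol gives neither input.
- **That the gain is free.** It needs a data field that is not listed.

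**What to change.** 1. In Randomization process, state how siblings are allocated: each infant separately, or the family as a unit.
2. In Measurements, add plurality and a coded mother identifier that links co-multiples and is exported with the patient identifier. This needs to be in place before data collection, because it may not be recoverable afterwards.
3. In Statistical analyses, fit the primary and secondary models with a random intercept for mother, alongside NICU and gestational age. Generalised least squares or GEE clustered on mother is an alternative. A robust standard error with an independence working correlation would correct validity but would not recover precision.
4. Keep plain regression as a sensitivity analysis, which would also show any pull from joint discharge.

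The cost is one linking field, a few sentences and slightly more analysis work, with no additional infants. If few multiples enrol, the two analyses will nearly coincide. The rounding of the effect size should be dealt with separately, in the sample-size section.

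### The protocol tests at α = 0.01 but presents group differences with 95% confidence intervals that are not labelled descriptive, so an interval could be read as positive when the test is not

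*Protocol*

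**What the plan says.** Two consecutive sentences in the protocol's Statistical analyses section set the test level and the interval level: "The significance level will be at α=0.01. Differences between the groups will be presented as mean with 95% CI". For categorical outcomes the section names odds ratios and gives no separate interval level.

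The Sample size section repeats the test level: "The statistical power is set at 0.90 and an alfa level equal to 0.01". Its planning values are a standardised effect of 0.3, attributed to earlier work, and on the scale of days, "considering a mean difference of 4 days between experimental and control group and a SD of 14". The stated result is 333 per group, which is then raised to 345 per group, 690 in total.

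The primary outcome is length of stay in days. The planned model for primary and secondary endpoints is linear regression with adjustment for confounders, so the p-value and the interval for an endpoint would come from one estimate and one standard error.

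The protocol plans no 99% interval. It does not say that the 95% interval is descriptive, or how to read an interval that excludes zero when p is above 0.01.

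**The concern.** When test and interval come from the same model, a two-sided test at level α rejects exactly when the 100(1 − α)% interval excludes zero. At α = 0.01 the matching interval is 99%. By fixing 95%, the protocol leaves a band of results, those with 0.01 < p < 0.05, that are not significant by its own criterion but are shown with an interval excluding zero.

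Many readers judge an effect by whether its interval crosses zero. For a result in that band, such a reader could conclude that length of stay differs between the groups although the protocol's criterion was not met. That reader would be applying a 5% criterion, five times the planned type I error rate. The same holds for any secondary endpoint judged at 0.01 and shown with a 95% interval.

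The mismatch runs one way only. From the same model, a 95% interval cannot include zero when p < 0.01.

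**Working it through.** **Step 1: is 0.01 the real design level?** The inputs from the Sample size section are standardised effect 0.3, power 0.90 and α = 0.01. The allocation ratio is 1:1. Sidedness is not stated.

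n per group = 2 (z_{1−α/2} + z_{power})² / d²

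- Two-sided 0.01, d = 0.3: 2 × (2.576 + 1.282)² / 0.09 = 331. The t-test version gives 332.3, which rounds up to the stated 333.
- One-sided 0.01, d = 0.3: 2 × (2.326 + 1.282)² / 0.09 = 290.
- 4 days with SD 14 (d = 0.286): 365 two-sided and 319 one-sided.

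Of these variants, only the two-sided calculation with d = 0.3 reproduces 333. So 0.01, two-sided, is the level the trial was sized for. (That 4/14 is 0.286 and not 0.3 is a separate matter and does not affect this point.) Even on a one-sided reading of 0.01, the matching two-sided interval would be 98%, still not 95%.

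**Step 2: the band on the primary outcome.** The inputs are the planned SD of 14 days and 345 per group, with no covariate adjustment.

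- SE = 14 × √(2/345) = 1.066 days
- 95% half-width = 1.960 × 1.066 = 2.09 days
- 99% half-width = 2.576 × 1.066 = 2.75 days
- Ratio = 2.576 / 1.960 = 1.31

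An observed difference between about 2.09 and 2.75 days, in either direction, gives a 95% interval that excludes zero and a test that is not significant at 0.01. With 333 per group the limits are 2.13 and 2.79 days.

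**Step 3: how often this would happen.** By the normal approximation, with θ = true difference / SE:

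P(p < a) = Φ(θ − z_{1−a/2}) + Φ(−θ − z_{1−a/2})

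P(0.01 < p < 0.05) = P(p < 0.05) − P(p < 0.01)

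| True difference (days) | P(p < 0.05) | P(p < 0.01) | P(0.01 < p < 0.05) |
|---|---|---|---|
| 0 | 5.0% | 1.0% | 4.0% |
| 2 | 46.7% | 24.2% | 22.5% |
| 2.5 | 65.0% | 40.9% | 24.1% |
| 3 | 80.4% | 59.4% | 20.9% |
| 4 (planned) | 96.3% | 88.0% | 8.3% |

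Under no effect, the 4% splits evenly between the two directions.

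**Step 4: sensitivity to covariate adjustment.** The planned regression is adjusted, and the protocol's Introduction says length of stay is strongly related to gestational age and birth weight. The residual SD should therefore be below 14. The protocol gives no R², so the values below are assumptions. Residual SD = 14 × √(1 − R²).

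| Assumed R² | SE (days) | Band (days) | At 0 days | At 2 days | At 3 days | At 4 days |
|---|---|---|---|---|---|---|
| 0 | 1.066 | 2.09 to 2.75 | 4% | 22% | 21% | 8% |
| 0.3 | 0.892 | 1.75 to 2.30 | 4% | 24% | 14% | 2% |
| 0.5 | 0.754 | 1.48 to 1.94 | 4% | 23% | 6% | 0.3% |

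Adjustment lowers the limits in days, and lowers the probabilities at 3 and 4 days. It leaves the 4% under no effect and the ratio of 1.31 unchanged.

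**The case against.** The strongest reply is that the protocol does not contradict itself. It has one decision rule, the test at 0.01, and the next sentence only says how differences will be displayed. A 95% interval is a valid estimate at its own level and may accompany a test at another level. A result with p = 0.03 has a single conclusion under the protocol: not significant. This stands, and it limits the point to presentation.

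A reader might go further and infer that the 1% error control is lost, or that the trial would be reported as positive on a failed test. The documents do not support either inference. Nothing makes the interval a decision rule, so the 0.01 test keeps its 1% error rate, and the power, sample size and estimate do not change. Misreading is a risk, not a certainty.

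The day limits are also open to challenge, because they use the raw SD although the planned analysis is adjusted. That is correct. The 2.09 to 2.75 day band is an unadjusted illustration, and at the planned 4-day effect the probability could be well below 8%. The 22% and 21% figures belong to true effects smaller than the one planned for.

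A last reply is that labelling of intervals can be left to a statistical analysis plan, which is not at hand. That is fair for the labelling. It does not cover the 95% level, which the protocol itself fixes directly after setting α at 0.01.

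**Conclusion.** The point holds as a reporting mismatch of minor to moderate severity. The only interval level the protocol names does not match the level at which it tests, and no text says which one governs the reading of a result with 0.01 < p < 0.05. In that band a reader relying on the interval could call the result positive, in effect at the 5% level.

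On the planning values the band is narrow in days. It would be reached with probability 4% under no effect and about 8% at the planned effect, and up to about 24% if the true effect is somewhat smaller than planned.

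These figures assume a two-sided test (inferred from the sample size), SD 14, 345 per group, no adjustment and the normal approximation. The mismatch itself depends on none of the numerical planning values.

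**What to change.** Amend the sentence on presentation in the Statistical analyses section in three respects:

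- Report the primary outcome, and any secondary endpoint judged at 0.01, with a 99% confidence interval. State the level for odds ratios as well.
- State that the test at α = 0.01, two-sided if that is what is intended, decides significance.
- Label any 95% interval also shown as descriptive.

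Stating that the test decides and that the 95% interval is descriptive would by itself remove the ambiguity. Adding the 99% interval also makes the displayed interval agree with the test.

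The cost is one or two sentences and intervals about 31% wider (2.576 / 1.960 = 1.31). On the unadjusted planning values the half-width goes from 2.09 to 2.75 days. No additional infants are needed, because the sample size was already computed at 0.01. The change should be made before the data are exported for analysis, so that the interval level is not chosen after the results are seen.

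### Side effects fall under the same model and the same α = 0.01 as the efficacy outcomes, which lowers the chance of detecting a true excess of harm

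*Protocol*

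**What the plan says.** Under Secondary outcomes, item 8 of the protocol's list is "side effects of treatment (osteopathy and clinical procedures)". It comes with no definition, unit of count or expected rate.

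Under Statistical analyses, the model for all outcomes is given in one sentence: "A generalized linear model, linear regression, will be considered to study the independent effect of OMT on primary endpoint and secondary endpoints". The threshold follows: "The significance level will be at α=0.01". Neither sentence sets safety apart. Results are to be shown as follows: "Differences between the groups will be presented as mean with 95% CI or in categories with OR for categorical data".

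The Sample size section rests on length of stay only. It states its assumptions as "effect size of 0.3 calculated from previous studies, considering a mean difference of 4 days between experimental and control group and a SD of 14", then adds: "The statistical power is set at 0.90 and an alfa level equal to 0.01". The planned number is 345 per group.

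Under Ethics and dissemination, the protocol states: "The expected disadvantages for the intervention provided in the trial are null". It says that no side effects of osteopathic care are predicted and cites one reference, whose title concerns paediatric patients. The next sentence commits the investigators to record any side effect and discuss it in the final paper.

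**The concern.** For efficacy, the error that a strict α prevents is a false claim that the treatment works. For harm, the more costly error is to overlook a true excess, and moving α from 0.05 to 0.01 makes that error more likely. The trial was sized on length of stay, so nothing in the design offsets the loss for event outcomes.

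The named model is also a poor fit. Whether an infant had a side effect is a yes/no outcome and may be rare. Linear regression does not yield the odds ratio that the same section promises for categorical data.

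What is at stake is the safety conclusion. The protocol starts from an expectation of no disadvantages, while its Introduction knows of only one published study of the treatment in preterm infants. A result above 0.01 could easily be taken as support for that expectation when the trial had little chance of showing otherwise.

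**Working it through.** **1. Reproduce the plan's own figure and settle the sidedness.** The protocol does not say whether α is one- or two-sided. With d = 0.3, α = 0.01 and power 0.90, n per group = 2(z_α + z_β)²/d².
- Two-sided: 2 × (2.576 + 1.282)²/0.09 ≈ 331. The version based on the noncentral t distribution gives exactly 333.
- One-sided: 2 × (2.326 + 1.282)²/0.09 ≈ 290.

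The protocol says: "This produces a sample size of 333 per group". Only the two-sided calculation reproduces this, so two-sided is used below.

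**2. Inputs for harm.** n = 345 per arm (Sample size section), allocation 1:1 (Randomization process), α = 0.01 (Statistical analyses), with 0.05 for comparison. The event rates are assumptions, because the protocol gives none. A doubling is examined over a range of control rates.

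**3. Formula, with one case worked.** With p̄ the mean of the two rates, power ≈ Φ{[(p₂ − p₁)√n − z√(2p̄(1 − p̄))] / √(p₁(1 − p₁) + p₂(1 − p₂))}.

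For 5% v 10%: 0.05 × √345 = 0.929; √(2 × 0.075 × 0.925) = 0.3725; denominator √(0.0475 + 0.09) = 0.371.
- α = 0.01: (0.929 − 2.576 × 0.3725)/0.371 = −0.083, so power is 46.7%.
- α = 0.05: (0.929 − 1.960 × 0.3725)/0.371 = 0.536, so power is 70.4%.

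**4. Exact check.** All pairs of binomial counts were enumerated with 345 per arm, using a pooled z-test and counting rejections in the direction of harm:

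| Control v treated | Power at 0.01 | Power at 0.05 |
|---|---|---|
| 2% v 4% | 14% | 34% |
| 3% v 6% | 24% | 48% |
| 5% v 10% | 47% | 71% |
| 7% v 14% | 67% | 86% |

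**5. Does the model or the α drive this?** For 5% v 10% at two-sided 0.01, exact power is 46.9% with the linear-regression t-test, 45.1% with a logistic Wald test and 41.9% with Fisher's exact test. At 0.05 the three are 71.3%, 70.7% and 66.0%. The loss comes from the threshold. The model is a separate problem, of fit and reporting.

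**6. No events at all.** With zero events among 345 treated infants, the one-sided 95% upper limit is 1 − 0.05^(1/345) = 0.86%. Even a clean record would leave a risk of that size possible.

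**The case against.** Several points on the other side stand.

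- **The rates are assumed.** A reader might infer that a doubling of side effects would be missed more often than found. The documents do not support that as a general statement. At two-sided 0.01, power for 5% v 10% is 46.9%, but for 5.5% v 11% it is already 52.6%, and for 10% v 20% it is 87.2%. Under a one-sided 0.01 test, 5% v 10% would have 57.2%. Item 8 also covers clinical procedures, so the base rate need not be low.
- **α is not the only limit.** For 2% v 4%, power is only 34% even at 0.05. For rare events the number of infants restricts detection, as in most trials sized for efficacy.
- **The model wording is loose.** The protocol says that the model will be considered, calls it a generalized linear model, and foresees an odds ratio for categorical data. That is not a firm commitment to linear regression for yes/no events. The passage still names one model and promises an output that this model does not give.
- **The statement on harm is an expectation.** A reader might infer that harm has been ruled out in advance. It has not: the text says what is expected and then commits to recording and discussing any side effect. No sentence says that p > 0.01 will be read as no side effects. A 95% interval, if given for this outcome, would show much of what a 0.01 test hides.
- **What parents are told is unknown.** The information sheet is not among the documents, so nothing can be concluded about its wording.
- **A statistical analysis plan may exist.** The choice of interval could properly sit there. The point here is narrower: the protocol states a rule, and as written it covers harm.

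**Conclusion.** The concern holds as a matter of a badly chosen rule. Side effects are a secondary outcome, and the single model and single threshold set for the secondary endpoints apply to them without exemption. Compared with 0.05, the 0.01 threshold costs roughly 19 to 24 percentage points of power across the doublings examined (34 − 14 = 20, 48 − 24 = 24, 71 − 47 = 24, 86 − 67 = 19).

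These figures rest on assumed event rates, 345 infants per arm analysed, and a two-sided test, which the sample size supports but the text does not state. They do not show that a given excess would usually be missed, since that depends on a rate the protocol does not supply. They do show that a non-significant result would be weak evidence for the expectation of no disadvantages, and weaker still for rare events. The primary analysis is unaffected.

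**What to change.** In Statistical analyses, exempt secondary outcome 8 from linear regression and from the 0.01 verdict. For this outcome:
- report the number of infants with at least one event in each arm, and the risk difference with an exact or score 95% confidence interval;
- if no events occur, give the upper limit (0.86%, one-sided 95%, for zero in 345);
- state that no conclusion of absence of side effects will be drawn from a p-value.

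In Ethics and dissemination, say that no side effects are expected but that the risk in preterm infants is not established. Keep the commitment to record and discuss any that occur.

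The cost is a few sentences in two sections, with no extra infants and no change to the primary analysis. The downside is a slightly higher chance of a false safety signal. If an interval excluding zero is taken as a signal, the nominal chance in the direction of harm rises from 0.01/2 = 0.5% to 0.05/2 = 2.5%.
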